**Figure 2 F0002:**
[figure not shown]
Sampling procedure of primary healthcare facilities with 640 clinicians, Guangdong Province, China, January 2026 – December 2026

In the second stage, all primary healthcare institutions under the jurisdiction of the recruited local health authorities in these three cities will be included in the sampling frame. These institutions will then be regrouped into PSUs based on the number of clinicians. This ensures that each unit has a sufficient number of clinicians, preventing the exclusion of smaller institutions from the sampling process. The PSUs will then be sampled using a probability proportional to size (PPS) sampling method.

The study will be conducted as a cluster-randomized trial. The intervention will be delivered to the entire cluster (PSU), but the intervention’s effect will be measured at the clinician level. The measurement is based on the average performance of a random sample of clinicians within the cluster. This is achieved through unannounced standardized patient (USP) visits, which function as the final step of the sampling process. A minimum of 80 USP visits will be assigned to each experimental condition.

*Sample size and power*

Power analyses were conducted to determine the sample size needed to test the effect of the implementation strategies on our primary outcome, ‘clinician advice to quit’. The detailed definition and measurement of this outcome are provided in the section on study outcomes. Based on prior research, the baseline rate for this outcome was 33.9%^13^. Through stakeholder consultation, it was determined that a 40% increase in delivery, resulting in a final primary outcome of 47.46%, would be considered a clinically meaningful effect. Assuming a two-tailed test with an alpha level of 0.05 and a desired power of 0.8, a sample size of 28 participants per cluster is required. Accounting for the cluster-randomized design with a design effect (Deff) of 2 and adjusting for an anticipated 20% loss to follow-up, the sample size has been intentionally increased to further enhance statistical power for detecting higher-order interactions. Consequently, the required sample size for one experimental condition is approximately 80 participants. Given our study design with eight conditions (one condition per PSU, for a total of eight PSUs), this translates to 640 participants in total.

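### The stated 28 participants per cluster does not follow from the plan's own inputs: a main effect needs 52–55, and 640 clinicians give about 60–70% power at the stated design effect, not 80%

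*Protocol article*

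**What the plan says.** The calculation is in the protocol article, Methods, Sample size and power, and concerns clinician advice to quit.

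- Control rate: "the baseline rate for this outcome was 33.9" per cent.
- Target: "a 40% increase in delivery, resulting in a final primary outcome of 47.46" per cent.
- Error rates and base result: "Assuming a two-tailed test with an alpha level of 0.05 and a desired power of 0.8, a sample size of 28 participants per cluster is" the number needed.
- Inflation: "a design effect (Deff) of 2 and adjusting for an anticipated 20% loss to follow-up".
- Further increase: "the sample size has been intentionally increased to further enhance statistical power for detecting higher-order interactions".
- Result: "the required sample size for one experimental condition is approximately 80 participants". With eight conditions and one PSU per condition, the total is 640.

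Two other places fix the contrast that the sample size must serve. Study design (Table 1) sets out a 2×2×2 factorial in which each technique is present in four conditions and absent in four. The last paragraph of Data analysis, under Qualitative analysis, says that statistically significant main effects will be used to identify the techniques that work.

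**The concern.** A difference of 13.56 percentage points between rates near 40% normally needs about 200 independent observations per arm. In a factorial trial an arm is a factor level, which here means four PSUs. Four times 28 is only 112, so the base figure looks too small before clustering is considered, and the later inflation starts from a base that is too low.

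The trial exists to decide which techniques to keep. If power for a main effect is well under 80%, a technique with exactly the effect that stakeholders called meaningful will miss significance more often than the one time in five that the paragraph implies. The same paragraph also gives the impression that the sample has something in hand for higher-order interactions.

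**Working it through.** **Inputs (Sample size and power).** p1 = 0.339; p2 = 0.339 × 1.4 = 0.4746, as stated; difference d = 0.1356; two-sided alpha 0.05 (z = 1.960); power 0.80 (z = 0.842); Deff 2; loss 20%; eight PSUs of 80. From Table 1: four PSUs per factor level.

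**1. The plan's own chain.** 28 × 2 / 0.8 = 70 per condition, raised to 80 (80/70 = 1.14, about 14% extra); 80 × 8 = 640. The steps after 28 are consistent. The 28 itself is the problem.

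**2. Base size per level.** With mean rate p = 0.4068:

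n = [1.960 × √(2p(1−p)) + 0.842 × √(p1(1−p1) + p2(1−p2))]² / d²

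= [1.960 × 0.6947 + 0.842 × 0.6881]² / 0.1356² = 204.8, so 205 per level.

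With continuity correction: (204.8/4) × [1 + √(1 + 4/(204.8 × 0.1356))]² = 219.3, so 220 per level.

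Per cluster, divide by four: 205/4 = 51.25, so 52; 220/4 = 55.

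Other two-sided formulas do not reach 28 either: unpooled 203, arcsine 205, log risk ratio 212 and log odds ratio 208 per level, all between 50 and 53 per cluster before rounding up. One-sided testing would need 162 (176 corrected) per level, or 41–44 per cluster.

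**3. What 28 per cluster delivers.** 28 × 4 = 112 per level. Power = Φ([d√n − 1.960 × 0.6947] / 0.6881) = Φ(0.107) = 54% (55% unpooled), with no clustering and no loss. Comparing one condition with one other, 28 against 28, gives 17%.

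**4. What 640 delivers at Deff 2.**

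| Situation | Effective n per level | Power, pooled | Power, unpooled |
|---|---|---|---|
| No loss, Deff 2 | 320/2 = 160 | 69.6% | 70.3% |
| 20% loss, Deff kept at 2 | 256/2 = 128 | 59.9% | 60.6% |
| 20% loss, ICC kept at 0.0127 | 256/1.80 = 142 | 64.5% | 65.2% |

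For the third row, Deff 2 at 80 per PSU implies ICC = (2 − 1)/79 = 0.0127. With 64 left per PSU, Deff = 1 + 63 × 0.0127 = 1.80.

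**5. What 80% power would take.** On the plan's inputs, 52 × 2 / 0.8 = 130 and 55 × 2 / 0.8 = 137.5, so about 130–138 per condition. Holding 640 fixed, the target rate detectable with 80% power (pooled formula) is 49.3% with no loss and 51.1% with 20% loss. Alternatively, 47.46% is detectable at 80% only if Deff is no more than 320/220 = 1.45 to 320/205 = 1.56 with no loss, or 256/220 = 1.16 to 256/205 = 1.25 with loss.

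**The case against.** **The formula and contrast are not shown.** This is true, and it limits what can be said about the cause. A reader might infer that the per-level number was spread over eight conditions instead of four, because 220/8 = 27.5 rounds up to 28. That match needs the continuity-corrected figure; the uncorrected 205/8 = 25.6 gives 26. Reading the increase as 40 percentage points (33.9% to 73.9%) with continuity correction also gives 28, although it contradicts the printed 47.46%. The documents do not settle the cause, and the shortfall does not depend on it.

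**The shortfall depends on Deff.** Without clustering, 640 would give 94% power with no loss and 88% after 20% loss. But Deff 2 is the plan's own assumption.

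**The power may be understated.** The Quantitative analysis section adjusts for baseline adherence and clinician characteristics. The sampling and outcomes sections set 80 standardized-patient visits per condition as a minimum and promise each clinician at least one. Either could add some precision. Neither is quantified or used in the sample-size paragraph, so the power range should be read as approximate. It does not rescue the 28.

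**The interaction sentence may be defensible.** A reader might call it untrue. That goes too far: 70 was raised to 80, which does add a little power, and no power level for interactions is promised. What fails is the implied reserve, because 640 falls short of 80% even for main effects.

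**Power may be much lower still.** With only eight PSUs a normal reference is optimistic, so a reader might put power well below 60%. How far below depends on degrees of freedom and an ICC that the document does not fix, so no lower figure is claimed here.

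**Conclusion.** The point stands as an error in a printed figure. From the stated rates, alpha and power, the base requirement is 52–55 per cluster, about twice the 28 given. With the stated Deff of 2, 640 clinicians give about 70% power per main effect if nobody is lost. After 20% loss they give about 60–65%: 60–61% if Deff stays at 2, about 65% if the implied ICC of 0.0127 is held constant. A technique with exactly the planned effect would then miss significance roughly 30–40% of the time, against the implied 20%.

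This rests on an unadjusted comparison of two proportions, equal PSU sizes, one analysed outcome per clinician and a normal reference. It is not an omission left to a statistical analysis plan, because the article prints both the inputs and a result that does not follow from them.

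**What to change.** In Sample size and power:

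1. Replace 28 with 52–55 per cluster before inflation, and name the contrast (main effect, four PSUs against four) and the formula.
2. For the fixed 640, state power of about 60–70% per main effect for 33.9% against 47.46%, or state that the rate detectable with 80% power is about 49–51%.
3. State the ICC behind Deff 2 and compute Deff at the actual PSU size. At 80 per PSU, Deff 2 corresponds to an ICC of 0.0127.
4. Remove the implication that 640 holds reserve power for higher-order interactions.

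The cost is one rewritten paragraph and a less favourable stated power. No additional enrolment is needed to make the statement correct.

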### Recruitment and informed consent

*Study setting*

The study will be conducted in primary healthcare institutions located in Guangdong Province, China, from January 2026 to December 2026. To ensure the generalizability of our findings across the diverse socioeconomic landscape of the country, we will strategically select institutions from three cities that represent a spectrum of economic development: a highly-developed city from the Pearl River Delta region, a moderately-developed city from either Eastern or Western Guangdong, and a less-developed city from Northern Guangdong. This deliberate selection allows us to rigorously test our implementation strategies under a wide range of conditions, from highly-resourced urban settings to more resource-constrained rural areas.

The selected institutions will include a variety of primary care settings, specifically community health service centers and township health centers/village health stations, to ensure a broad representation of primary care delivery models. We will recruit a sufficient number of institutions to meet the sample size requirements determined in the section sample size and power.

The institutional inclusion criteria are as follows: 1) the institution must have been a member of a compact medical consortium within the last three years; and 2) the institution must provide comprehensive primary healthcare services. The exclusion criteria for institutions include: 1) ongoing participation in any other smoking cessation intervention studies; and 2) ongoing participation in other implementation studies that are testing any of the specific implementation techniques used in our trial.

*Study population*

The study population is clinicians, encompassing licensed clinicians, licensed assistant clinicians, and certified village clinicians. Clinicians will be included based on the following criteria: 1) they have worked in a clinical capacity for at least six months; and 2) they provide outpatient and primary healthcare services. Conversely, clinicians will be excluded if they meet any of the following criteria: 1) they have previously received smoking cessation-related training or participated in a similar trial; 2) they are absent from work for one month or more; 3) they are a non-formal employee such as a temporary worker or rotational staff; and 4) they are currently participating in other studies related to any of the specific implementation techniques being tested in the present trial.

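### With eight fixed PSUs, the planned 640 clinicians do not give the stated 80% power under either possible meaning of the design effect of 2, and the ICC behind it is not stated

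*Protocol article*

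**What the plan says.** All the figures stand in the protocol article under Sample size and power. The test is fixed as follows: "Assuming a two-tailed test with an alpha level of 0.05 and a desired power of 0.8". The outcome is clinician advice to quit, with a baseline rate of 33.9% and "a 40% increase in delivery, resulting in a final primary outcome of 47.46" per cent as the target. From these the plan concludes that "a sample size of 28 participants per cluster is required".

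The inflation comes next: "Accounting for the cluster-randomized design with a design effect (Deff) of 2 and adjusting for an anticipated 20% loss to follow-up". A further deliberate increase is made for higher-order interactions, and "the required sample size for one experimental condition is approximately 80 participants". There is one PSU per condition, so eight PSUs and 640 clinicians in total.

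The Sampling procedure section makes the PSU the unit of randomization, and Quantitative analysis clusters the GEE at PSU level. No ICC is given.

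**The concern.** All the inflation goes into the size of the eight PSUs and none into their number. The design effect is 1 + (m − 1) × ICC, so it grows with the cluster size m. A value of 2 can be multiplied into the cluster size only if it was evaluated at the size finally reached, and the paragraph does not say whether it was. The PSUs come from "three cities that represent a spectrum of economic development", so a near-zero ICC cannot be taken for granted.

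The power matters for the trial's decision. The closing paragraph of the Data analysis section picks techniques by whether their main effects are statistically significant and positive. If the real power is well below 0.8, a technique with exactly the targeted effect could easily be dropped from the optimal set.

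**Working it through.** **Inputs from Sample size and power.** p1 = 0.339; p2 = 0.339 × 1.40 = 0.4746; d = 0.1356; two-sided 0.05; power 0.8; 28 per cluster; design effect (Deff) 2; loss 20%; about 80 per PSU; eight PSUs. In a 2×2×2 factorial each main effect compares four PSUs with four. The analysed cluster size m is 80, or 80 × 0.8 = 64 after the planned loss. The ICC is not given and is treated as an assumption.

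**The plan's own figures.** 28 × 2 = 56; 56 / 0.8 = 70; the step from 70 to about 80 is the stated extra increase; 80 × 8 = 640. The inflation reproduces. The 28 does not: a two-proportion calculation on the stated rates gives 205 per factor level (220 with continuity correction), which is 205 / 4 = 51 (or 55) per PSU before any design effect.

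**Formulas.** Deff = 1 + (m − 1) × ICC. Effective size per PSU = m / Deff. N per level = 4m / Deff. SE = √[(p1q1 + p2q2) / N], with p1q1 + p2q2 = 0.2241 + 0.2494 = 0.4734. Power = Φ(d / SE − 1.96). A pooled variance changes the powers by about one percentage point.

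**What 28 effective clinicians per PSU would give.** N = 112, SE = 0.0650, d / SE = 2.09, power 55% (54% with pooled variance).

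**Reading A: Deff 2 holds at the final size.**
- m = 80: ICC = 1/79 = 0.013; effective 40 per PSU; N = 160; SE = 0.0544; d / SE = 2.49; power 70%.
- m = 64: ICC = 1/63 = 0.016; effective 32 per PSU; N = 128; SE = 0.0608; d / SE = 2.23; power 61%.

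Both exceed 28 effective, and neither reaches 80%.

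**Reading B: Deff 2 holds at m = 28.** ICC = 1/27 = 0.037.
- m = 80: Deff = 1 + 79/27 = 3.93; effective 20.4; N = 81.5; SE = 0.0762; power 43%.
- m = 64: Deff = 1 + 63/27 = 3.33; effective 19.2; N = 76.8; SE = 0.0785; power 41%.

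As m grows, m / Deff approaches 1 / ICC = 27, so at this ICC no cluster size reaches 28 effective.

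**Range of assumed ICC.** The detectable difference is the rise from 33.9% that has 80% power.

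| ICC | Power, m = 80 | Power, m = 64 | Detectable difference, m = 64 |
|---|---|---|---|
| 0 | 94% | 88% | 12 points |
| 0.013 (1/79) | 70% | 65% | 16 points |
| 0.016 (1/63) | 65% | 61% | 17 points |
| 0.020 | 59% | 56% | 18 points |
| 0.037 (1/27) | 43% | 41% | 22 points |
| 0.05 | 35% | 34% | 24 points |
| 0.10 | 22% | 21% | 32 points |

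The plan's target difference is 13.56 points.

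**Two different ICC limits.**
- For 80% power, about 51.25 effective per PSU are needed. The limit is (64 / 51.25 − 1) / 63 = 0.004 at m = 64 and (80 / 51.25 − 1) / 79 = 0.007 at m = 80.
- For 28 effective per PSU, the limit is (64 / 28 − 1) / 63 = 0.020 at m = 64 and (80 / 28 − 1) / 79 = 0.024 at m = 80.

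**Few clusters.** The normal approximation ignores that only eight PSUs carry the comparison. With a t reference on 6 degrees of freedom (eight PSUs less two group means), power at m = 64 is 75% even at ICC 0. At m = 80 it reaches 80% only for an ICC up to about 0.001. A model with all main and interaction effects would leave no between-PSU degrees of freedom at all.

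**The case against.** The strongest reply is that multiplying by a design effect is standard practice when it is evaluated at the planned cluster size, and that the paragraph never ties the 2 to a cluster of 28. That stands. A reader might infer that the inflation step is an outright error, or that an ICC of 0.037 is the plan's own assumption. The text supports neither. On Reading A the step is coherent and meets the plan's target of 28 effective clinicians per PSU; the shortfall there comes from 28 being too low for the stated rates. The powers above therefore carry that error as well, and should not be charged to the design effect alone.

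A reader might also infer that an ICC up to about 0.02 keeps the 80% power. It does not: 0.020 to 0.024 is the limit for 28 effective clinicians, and power at 0.020 is already 56% to 59%.

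A condensed article may leave the ICC to the full protocol, so its absence alone would be no finding. Here, however, the printed inputs fail to give the printed power on either reading. Adjustment for baseline adherence and clinician covariates could lower the residual ICC, and a PSU that regroups several facilities need not have the correlation of a single facility. Both could help, but no figure is given for either. The ICC would have to be below about 0.007, and the few-cluster correction works the other way.

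**Conclusion.** The concern holds in this form: the sample-size paragraph does not support its claim of 80% power for a main effect, whichever cluster size its design effect of 2 refers to. Power is about 61% to 70% if the 2 holds at the final size, and about 41% to 43% if it holds at 28 per cluster. On the stated rates, 80% needs an ICC of at most about 0.004 to 0.007, before any allowance for few clusters.

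This rests on a four-versus-four comparison of PSUs, equal PSU sizes, the stated rates, no gain from covariates and a normal approximation. The last of these favours the plan. The documents give no ICC, so values other than 0.013, 0.016 and 0.037, which follow from the plan's own figures, are assumptions. Which reading was intended cannot be settled from the text.

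**What to change.** - State the assumed ICC and its source, and compute the design effect as 1 + (m − 1) × ICC at the analysed cluster size of 64 to 80.
- Replace the 80% power statement with the resulting power or detectable difference over a stated ICC range, such as 0.01 to 0.10. Work from 33.9% and 47.46%, not from the figure of 28, and say that the normal approximation is optimistic with eight PSUs.
- Report with the results the ICC estimated from the endline USP data. An ICC from baseline would be only a rough guide: the footnote to Table 2 places USP visits at endline and the limitations describe them as a single time point, so baseline data would presumably come from patient callbacks.
- State in the decision rule for the optimal set that a non-significant main effect is not evidence that a technique does not work.

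The cost is a rewritten paragraph and a short calculation, with no extra clinicians or visits. The downside is a less favourable stated power. This corrects the claim but does not restore the power: once the ICC exceeds about 0.02, more clinicians within the same eight PSUs cannot bring a main effect to 80%, since the effective size per PSU stays below 1 / ICC, which is under the 51 needed.

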## METHODS

### Study design

*Hybrid and full factorial design*

This study is designed as a type 3 hybrid implementation trial^14^, concentrating on the development and assessment of the effectiveness of a specific implementation strategy to enhance the adoption and implementation of BISC. The design prioritizes the evaluation of implementation strategies while also examining clinical outcomes. The research adheres to the principles of the Multiphase Optimization Strategy (MOST)^15,16^ with its core component being a 2×2×2 full factorial design (Figure 1). This design will result in eight distinct experimental conditions and allows for the evaluation of the main effects and potential interaction effects of the implementation techniques, which is the core purpose of the optimization trial. The study has identified four key implementation techniques to be included in the trial. One of these, assessing readiness and identifying barriers and facilitators, will be included as a constant component in all eight conditions, ensuring a foundational level of support for all participants. The remaining three techniques serve as the three factors of the factorial design, each with two levels (present or absent) (Table 1).

**Table 1 T0001:** Full factorial design (2×2×2) with constant components within a type 3 hybrid effectiveness-implementation trial of BISC in primary healthcare facilities with a sample of 640 clinicians, Guangdong, China, January 2026 – December 2026

*Experiment* *conditions*	*Constant component*	*Optional components to be tested*		
	*Assess for readiness and* *identify barriers and* *facilitators*	*Identify and prepare* *champions*	*Alter incentive/allowance* *structures*	*Conduct educational* *meetings*
1	Yes			
2	Yes	Yes		
3	Yes	Yes	Yes	
4	Yes	Yes		Yes
5	Yes		Yes	
6	Yes		Yes	Yes
7	Yes			Yes
8	Yes	Yes	Yes	Yes

Yes: means included in intervention. No: means not included in intervention. The specifics form (such as ‘ranking primary healthcare clinicians’ execution of BISC and providing spiritual rewards for excellence’) of each component (such as ‘Alter incentive/allowance structures’) will be developed by inviting stakeholders to work together, following the principles of co-production. BISC: brief intervention for smoking cessation.

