*Sampling procedure*

This study will use a multistage, clustered sample design. The primary sampling unit (PSU), which is a regrouped unit of clinics or facilities, will serve as the randomization unit. The sampling process will be conducted in multiple stages (Figure 2). The first stage involves the purposive selection of three cities within Guangdong province to ensure a comprehensive representation of different socioeconomic development levels. Specifically, we will select one highly-developed city from the Pearl River Delta region, one moderately-developed city from either Eastern or Western Guangdong, and one less-developed city from Northern Guangdong.

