### Data analysis

*Quantitative analysis*

Data will undergo de-identification prior to analysis. Baseline characteristics of participants will be presented, utilizing mean and standard deviation for continuous variables and frequency and percentage for categorical variables. The trial outcome analysis will adhere to the intent-to-treat principle. Generalized estimating equations (GEE) with a binomial distribution and log link function will be used for the primary binary outcome, with clustering specified at the PSU level, to assess the main and interaction effects of the four implementation techniques on adherence to BISC practices among primary healthcare clinicians. The model will account for robust predictors of outcomes, including baseline adherence scores and sociodemographic factors of clinicians^24-26^. Effect coding will be applied to each experimental condition, and subgroup analyses based on age, gender, clinician level, and facility will be conducted to further explore the impact of different technique combinations on BISC implementation. Sensitivity analyses, involving imputation of missing values through random forest, will be performed to validate the robustness of the findings^27^. For continuous outcomes, GEE models with a Gaussian distribution and identity link function will be employed, adjusting for the same covariates and clustering at the PSU level. In the analysis, control for covariates including clinician-related information (gender, age, professional title, and department) and patient-related information (gender, age, primary diagnosis, and smoking status). We will perform subgroup analyses on patient smoking status, level of tobacco dependence, and clinician department to investigate differences in BISC implementation among different types of clinicians for various types of patients.

Hypothesis tests will be two-sided, with statistical significance set at p<0.05. All statistical analyses will be performed using Stata version 16.0 and R version 4.5.2.

*Qualitative analysis*

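### With one PSU per condition, the planned PSU-clustered GEE with interactions has no between-PSU error term; only main effects can be tested, on 4 degrees of freedom, if interactions are assumed absent

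*Protocol article*

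**What the plan says.** The Sampling procedure section defines the PSU as a unit "which is a regrouped unit of clinics or facilities, will serve as the randomization unit". It adds: "The intervention will be delivered to the entire cluster (PSU), but the intervention’s effect will be measured at the clinician level". PSUs are built for the study: "These institutions will then be regrouped into PSUs based on the number of clinicians". The Sample size and power section fixes the number of clusters as "one condition per PSU, for a total of eight PSUs", with about 80 clinicians in each and 640 in all. It also says that the sample was enlarged to help detect higher-order interactions.

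The Study design section states that the factorial "allows for the evaluation of the main effects and potential interaction effects of the implementation techniques" and treats this as the core purpose of the trial. The Quantitative analysis section names a log-binomial GEE as the primary model and describes its scope in these words: "with clustering specified at the PSU level, to assess the main and interaction effects of the four implementation techniques". The Qualitative analysis section bases the choice of techniques on statistically significant main effects, with interactions also considered.

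The article nowhere gives a second PSU per condition, a small-sample correction, or a restriction to main effects.

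**The concern.** In a cluster-randomized factorial trial, the error for any factorial effect must come from variation between clusters that received the same condition. With one cluster per condition there is no such variation to observe. A difference between two conditions may equally be a difference between two PSUs in place, staffing or patient mix. More clinicians per PSU do not help, because they sharpen each PSU's mean without showing how PSUs differ under the same condition.

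At stake is the trial's decision rule. Techniques are to be kept or dropped on p-values, and interactions are to be read as synergy or antagonism. If the standard errors are spuriously small, ordinary differences between PSUs will be reported as effects of techniques. No analysis after data collection can supply the missing replication.

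**Working it through.** **1. Inputs.** From the article: 8 conditions; 1 PSU per condition; about 80 clinicians per PSU; rates 0.339 and 0.4746; two-sided alpha 0.05; power 0.80; Deff 2; 20% loss. No ICC is stated.

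**2. The plan's own figures.** 8 × 80 = 640 reproduces. The inflation 28 × 2 / 0.8 gives 70, and the text attributes the rise to 80 to a deliberate increase. The 28 per cluster does not reproduce: the standard two-proportion formula for 33.9% versus 47.46% gives 205 per comparison group. That is a separate matter, and nothing below depends on it.

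**3. Degrees of freedom** (PSUs minus factorial parameters).
- Full model: 1 intercept + 3 main + 3 two-way + 1 three-way = 8, so 8 − 8 = 0.
- Without the three-way term: 8 − 7 = 1.
- Main effects only: 8 − 4 = 4.

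**4. What the planned model returns.** With 8 columns on 8 PSUs, the fit reproduces every PSU mean. Each PSU's residuals sum to zero, and so does the robust variance. A log-binomial GEE with 8 groups of 80 gave robust standard errors below 1e-15 for every coefficient. Adding one simulated clinician covariate gave about 0.000 to 0.003, which is still unusable.

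**5. Type I error of the alternatives** (4,000 simulated null trials per setting, 8 PSUs of 80).
- Robust z-test, main effects plus two-way interactions: about 61–62%.
- Robust z-test, main effects only: about 23–25%. Both results hardly change over ICC 0.005 to 0.05.
- Model-based standard errors that ignore clustering: 9%, 17%, 33% and 52% at ICC 0.005, 0.0127, 0.037 and 0.10.
- Cluster-level t-test on 4 df, main effects only, all interactions truly zero: about 5%.

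**6. Assumed ICCs.** From Deff = 1 + (m − 1) × ICC, Deff 2 implies 1/79 = 0.0127 at m = 80 and 1/27 = 0.037 at m = 28. Both are shown, with 0.005 and 0.05 as outer values.

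**7. Power for a main effect.** With k PSUs per condition and m clinicians per PSU, V = [p1(1 − p1) + p2(1 − p2)] × Deff / (4km). The noncentrality is 0.1356/√V, referred to a noncentral t. The bracket is 0.2241 + 0.2494 = 0.4734.

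Example, 8 PSUs at ICC 0.0127: V = 0.4734 × 2.00/320 = 0.00296; noncentrality 2.49; critical t on 4 df 2.776; power 0.475.

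Example, 24 PSUs of 26.67 at the same ICC: Deff = 1 + 25.67 × 0.0127 = 1.32; V = 0.00196; noncentrality 3.06; critical t on 16 df 2.120; power 0.82.

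| ICC | 8 PSUs, main effects only, 4 df | 24 PSUs, full model, 16 df | 24 PSUs after 20% loss |
|---|---|---|---|
| 0.005 | 62% | 88% | 81% |
| 0.0127 | 48% | 82% | 75% |
| 0.037 | 28% | 66% | 61% |
| 0.05 | 23% | 59% | 55% |

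**The case against.** A reader might infer that no main effect can be tested at all, because condition and PSU coincide. The design does not support that. Each level of a factor covers four PSUs, so a main effect has a valid standard error on 4 df once interactions are assumed zero. This is a real limit on the point. It is not the planned analysis, however, and it gives up the aim that the article calls the core purpose.

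A reader might also infer that the trial will report standard errors of exactly zero and reject every null. That describes the model without covariates. The article adjusts for baseline adherence and for clinician and patient characteristics, and it does not say outright that the three-way term will be fitted, although its mention of higher-order interactions points that way. Adjustment makes the standard errors non-zero but not meaningful, and dropping the three-way term leaves a single degree of freedom.

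A third objection concerns the remedy. Its 82% power depends on a single assumed ICC, and at 0.037 or 0.05 it falls to 66% or 59%. The calculation also keeps the ICC constant although the PSUs become a third of the size. Regrouping requires that allocation has not yet taken place. The study window is January to December 2026, the article is dated March 2026, and the readiness assessment is described in the past tense, so the status is unclear. Several components act on whole institutions, and no institution count is given. All of this stands. It limits what the remedy can promise but leaves the defect untouched.

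**Conclusion.** The point holds. With eight PSUs in eight conditions, the planned GEE with interactions has up to 8 factorial parameters on 8 clusters and no between-PSU error term. Interactions cannot be tested validly unless other interactions are assumed zero.

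Main effects can be tested only on the assumption of no interactions. The usual robust z-test then has a type I error of about 25% instead of 5%. The valid t-test on 4 df has roughly 23% to 62% power over ICC 0.05 to 0.005, against the planned 80%.

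The failure of the model follows from the counts alone and needs no ICC. The power figures do rest on assumed ICCs, equal PSU sizes and the article's two rates. This should be settled before allocation if that is still possible, because the selection of techniques depends on these tests.

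**What to change.** **If allocation has not happened and each city has enough separate institutions:** regroup the same 640 clinicians into more, smaller PSUs, for example 24 of about 27, three per condition with one in each city, and randomize those. Fit three main effects, three two-way interactions and one three-way interaction, with a small-sample-corrected variance and a t reference on PSU degrees of freedom. State the assumed ICC and restate power as a range, about 59% to 88% (55% to 81% after 20% loss), not as 80%. The cost is a protocol amendment, more coordination and some contamination risk between neighbouring PSUs. No extra clinicians or standardized-patient visits are needed.

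**If eight PSUs must stay or are already allocated:** restrict the confirmatory analysis to the three main effects, using PSU-level summaries and a t-test on 4 df. State the assumption of no interactions and the reduced power. Withdraw the claim that interactions can be tested, and present any interaction estimates as descriptive only. This costs only a change of text and analysis.

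**Minor, in either case:** the Quantitative analysis section should refer to three tested techniques. The fourth is constant in all conditions, so its effect cannot be estimated.
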